### Cost analysis

If possible, the costs of National Health Service (NHS) primary care hypertension management including both medical consultations and antihypertensive prescriptions between the patient groups with and without the implementation of the digital intervention will be compared before and after the implementation period. The impact on NHS cost from implementation of Hypertension-Plus will be examined by comparing both before and after and between the intervention and the no-intervention groups. Data are likely to be limited due to inconsistencies in practice and practitioner level recording of activity and a decision will be made following data extraction if sufficient data are available to undertake these analyses.

### Digital Intervention data outcomes and analysis

#### Digital intervention outcomes

For the data extracted directly from Hypertension-Plus, the outcomes of interest will be:

1) the mean change in home SBP level comparing baseline BP (first week of measurement) with BP in (or next available after) the 6th month of measurement.

2) the number/proportion of people who initially onboarded that subsequently measure their BP and transmit it to the system at least once and time (days) between onboarding and first recorded measurement.

3) the mean change in home DBP level from baseline after the 6 months of home BP telemonitoring, comparing baseline BP with BP in (or next available after) the 6th month of measurement.

Depending on data availability we will do more exploratory analyses on:

Subgroups: outcomes 1–3 will be assessed in 10-year age intervals.

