### The intervention

The digital intervention (“Hypertension Plus”) was provided by Omron Healthcare combining blood pressure telemonitoring with prompts for hypertension management including medication titration intended to facilitate remote care [4]. The intervention is based on workflow algorithms developed from research data and decision support tools designed to be compliant with National Institute for Health and Care Excellence (NICE) guidelines [8].

The system combines a web-based dashboard for professionals, which both reads and writes data to the practice clinical system, with a mobile phone “app” which is downloaded by participating patients and used to upload BP readings. Patients are invited to use the digital intervention via contact from their practice and then sign up via a bespoke web interface. The choice of which patients receive an invitation is at the discretion of practices, but they are typically people with raised BP receiving antihypertensive treatment plus some without a diagnosis of hypertension. Telephone and online support is provided for those people having problems accessing or engaging with the technological platforms.

The digital intervention is a commercial system and is licenced annually, usually at local healthcare organisation level (known as primary care networks (PCN) or Integrated Care Boards in England). Implementation is being led by Omron working with the National Association for Primary Care (NAPC, https://napc.co.uk) and includes training for practices, support with identification of appropriate groups, support for patients, and peer led support facilitated by the NAPC.

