### Exploratory outcomes

Exploratory outcomes include the evaluation of the impact of the digital intervention on antihypertensive medication use and other cardiovascular preventative treatment (statins, antiplatelets, anticoagulants). Subgroups (see below) will be examined for the comparisons defined in the primary outcome.

Further exploratory outcomes will be addressed using the standalone intervention data. These are detailed below in the Hypertension-Plus outcomes and analysis section.

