### Statistical analysis

Descriptive statistics will be presented as the means and standard deviation (SD), proportions, and medians with interquartile ranges where appropriate. In the efficacy analyses for blood pressure, mixed-effects model repeated measures will be used to compare the changes in BP for people on the hypertension registers (i.e. with a clinical code for hypertension) between one year before and one year after implementation of the digital intervention within each practice. Fixed effects in the model are the exposure, whether BPs are measured (home or clinic), periods (12 months before and after implementation), interaction terms between the exposure and time period variable and covariates that were selected a priori because they have been reported to show correlations with both BP and cardiovascular (CVD) risk and could potentially confound the association between BP and CVD risk. These potential confounders will include baseline demographic characteristics (age, sex, ethnicity, IMD and frailty), clinical characteristics at baseline (SBP and DBP, total cholesterol, smoking, antihypertensive medication use), past history (diabetes, established cardiovascular disease, and chronic kidney disease). Random effects for patient and practice level average BP will also be included in the model. These covariates were selected a priori because they have been reported to show correlations with both BP and CVD risk and could potentially confound the association between BP and CVD risk [12]. Covariates are defined using the closest available electronic healthcare records data prior to baseline. The intervention analysis will take a similar approach albeit limited to the self-monitoring group and the variables included in the Hypertension-Plus dataset.

A 5% significance level will be used for all analyses/ tests.

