### Statistical analysis of Digital Intervention data

Baseline BP will be defined as the mean BP of the first BP measurement cycle. BP at 6 months will be defined as the mean BP value corresponding to the cycle 6 months after the first measurement cycle (or the next available data after 6 months if data after 6 months is not available). In the efficacy analyses for BP, mixed-effects model repeated measures will be used to compare the changes in BP from baseline to 6 months. Baseline patients’ characteristic will be set as fixed effects and registered GP practice and patient as random effects in this model. Baseline patients’ characteristics include demographic variables (age, gender, ethnicity, frailty and multimorbidity), past history (type 2 diabetes, chronic kidney disease or type 1 diabetes, renal disease, heart failure, cardiovascular (CVD) event, increased CVD risk [estimated 10 years], and postural BP drops) and antihypertensive medication use.

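### The exploratory six-month home BP change among Hypertension-Plus users may be confounded with season unless onboarding is spread evenly over the year

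*Protocol article*

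**What the plan says.** The protocol article defines outcome 1 as "the mean change in home SBP level comparing baseline BP (first week of measurement) with BP in (or next available after) the 6th month", and outcome 3 likewise for diastolic pressure. The section Statistical analysis of Digital Intervention data defines follow-up as "the mean BP value corresponding to the cycle 6 months after the first measurement cycle", with a fallback to later data where that cycle is missing.

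The contrast has no comparison group. The section Statistical analysis describes it as "albeit limited to the self-monitoring group and the variables included in the Hypertension-Plus dataset". The model is stated: "In the efficacy analyses for BP, mixed-effects model repeated measures will be used to compare the changes in BP from baseline to 6 months". Its terms are given too: the patients' characteristics at the start "will be set as fixed effects and registered GP practice and patient as random effects in this model". The characteristics listed are demographic variables, past history and antihypertensive medication use; no month, season or date is among them.

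These outcomes rank below the primary one: "Further exploratory outcomes will be addressed using the standalone intervention data" (Exploratory outcomes). The primary model, by contrast, has "periods (12 months before and after implementation), interaction terms between the exposure and time period variable", and compares people invited with people not invited.

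**The concern.** Blood pressure may vary over the year. If it does, two readings about six months apart differ by season as well as by time on the system. A before-after contrast in users alone attributes that difference to time on the system unless the design or the model removes it.

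Neither does so here. Covariates fixed at baseline, and random effects for a patient's or practice's level, describe where someone starts; they do not describe a shift within the same person between two calendar dates. The primary analysis has two protections that this one lacks: each window covers a full year, and a not-invited group lives through the same calendar time.

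If onboarding fell mostly near the seasonal peak, home pressure would appear to fall with no intervention effect. If it fell mostly near the trough, a real fall would be understated or hidden. Because the analysis is labelled one of efficacy, a reader could take the seasonal part as effect.

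**Working it through.** **Figures in the protocol.** It states no expected change, sample size or power for the six-month outcomes, so there is no figure to reproduce. The only yardstick is the 3 mmHg effect in Sample size, which was set for the primary comparison. The lag (about 5 to 6 months, or longer under the next-available rule) and the model terms come from the sections cited above.

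**Assumptions, not in the documents.** Home SBP follows an annual cosine with peak-to-trough swing D = 2, 4 or 6 mmHg. Onboarding is uniform over a window of W months centred c months after the peak. There is no true effect.

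**Formula.** For lag L months, the spurious mean change is

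(D/2) × a(W) × [cos(2π(c+L)/12) − cos(2πc/12)], with a(W) = sin(πW/12)/(πW/12).

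At L = 6 this becomes −D × a(W) × cos(2πc/12), so at six months the whole swing can enter.

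**Onboarding centred on the peak (c = 0), L = 6, in mmHg:**

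| Window | a(W) | D = 2 | D = 4 | D = 6 |
|---|---|---|---|---|
| Single date | 1 | −2.0 | −4.0 | −6.0 |
| 3 months | 0.900 | −1.8 | −3.6 | −5.4 |
| 6 months | 0.637 | −1.3 | −2.5 | −3.8 |
| 9 months | 0.300 | −0.6 | −1.2 | −1.8 |
| 12 months | 0 | 0 | 0 | 0 |

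**Other centres (D = 4, W = 3, L = 6).** Peak −3.6; one month later −3.1; two months −1.8; three months 0; trough +3.6.

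**Other lags (D = 4, single date at the peak).** −3.7 at 5 months, −4.0 at 6, −3.0 at 8, −2.0 at 9. Later readings therefore shrink the shift for peak onboarding. The zero at midway centring is specific to a six-month lag: for c = 3 and L = 9 the formula gives 2 × (1 − 0) = +2.0.

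**Primary analysis.** The same cosine averaged over 12 full months before and 12 full months after gives a difference of 0.

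**What a small shift would do.** Take n = 800 users for illustration. With the protocol's measurement SD of 10 mmHg, the SD of change is 10 × √(1/1 + 1/1) = 14.14 for one reading at each end, or 10 × √(1/2 + 1/2) = 10 for two. The standard errors are 14.14/√800 = 0.50 and 10/√800 = 0.354. With a seasonal shift of 1 mmHg and no true effect, the chance of p < 0.05 is Φ(1/SE − 1.96) + Φ(−1/SE − 1.96), which is 52% and 81%.

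**Does a calendar term help?** Simulation: 600 patients, monthly cycles, cycle SD 5 mmHg, true change −3 mmHg, swing 3 mmHg, peak-centred onboarding, 200 runs (all assumed). With a six-month window, the plain first-to-sixth-month difference averaged −4.9. With annual sine/cosine terms fitted to all cycles the estimate averaged −3.0, and its standard error rose from about 0.3 to 0.4. With a three-month window the adjusted standard error was about 0.85. The data were generated with the same cosine that the model fits, which favours the adjusted estimate.

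**The case against.** The strongest reply is that nothing in the document shows an error. It gives no onboarding dates. It says that practices choose whom to invite and that patients then sign up, which is compatible with onboarding spread over the year. The amplitude is borrowed from outside, and centring on the peak is the least favourable case. The outcomes are exploratory, and the effect question is answered by the primary analysis. A month term is also a detail that a condensed article might leave to a fuller plan.

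Most of this stands, and it rules out several stronger readings:

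- A reader might infer that seasonal change is counted as intervention effect. That holds only if onboarding is uneven; the shift can be zero or of either sign.
- A reader might infer that every pair of readings lies in opposite seasons. The next-available rule lengthens some lags.
- A reader might infer that patients joined in roll-out waves. The article says "Implementation is being led by Omron working with the National Association for Primary Care", which tells us who led the work, not when patients joined.
- A reader might judge the result against a 3 mmHg target. That figure belongs to the primary sample size; no target is set for this change.
- A reader might assume that calendar dates are in the extract. Outcome 2 needs days from onboarding to first measurement, but the article does not say that dates are supplied.

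The point about level of detail does not stand. The article writes out the contrast, the lag, the users-only population, the covariates and the efficacy label. Followed as written, they leave any net seasonal change inside the estimate.

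**Conclusion.** The concern holds as a conditional one. As specified, outcomes 1 and 3 cannot separate a net seasonal change from change on the system, and whether there is a net seasonal change depends on onboarding dates that the article does not give. For SBP, under an assumed annual swing of 2 to 6 mmHg and a six-month lag, the spurious change is 0 with even onboarding or with onboarding centred midway between peak and trough. It reaches about 1.8 to 5.4 mmHg, down or up, with a three-month window centred on the peak or trough. The diastolic outcome has the same structure; its size was not worked out. This is a cheap improvement to an exploratory analysis. The primary 12-month comparison is not affected.

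**What to change.** Where calendar dates of readings are available:

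- Fit the Hypertension-Plus mixed model to all transmitted cycles, with time since first cycle plus calendar-month or annual sine/cosine terms.
- Report the season-adjusted six-month change beside the planned unadjusted one.
- Tabulate onboarding by calendar month.
- Add a 12-month, same-season change where data exist.

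In all cases, describe the result as change among users, not efficacy.

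The work is analysis wording and a few lines of code, provided the extract carries dates; this should be confirmed first. The price is precision, modest at a six-month spread but nearly a threefold standard error at three months in the simulation above. If onboarding falls within about three months, state that season and effect cannot be separated well; adjustment helps least where the risk is greatest.

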### Statistical analysis of Digital Intervention data

Baseline BP will be defined as the mean BP of the first BP measurement cycle. BP at 6 months will be defined as the mean BP value corresponding to the cycle 6 months after the first measurement cycle (or the next available data after 6 months if data after 6 months is not available). In the efficacy analyses for BP, mixed-effects model repeated measures will be used to compare the changes in BP from baseline to 6 months. Baseline patients’ characteristic will be set as fixed effects and registered GP practice and patient as random effects in this model. Baseline patients’ characteristics include demographic variables (age, gender, ethnicity, frailty and multimorbidity), past history (type 2 diabetes, chronic kidney disease or type 1 diabetes, renal disease, heart failure, cardiovascular (CVD) event, increased CVD risk [estimated 10 years], and postural BP drops) and antihypertensive medication use.

### Qualitative study

Guided by the ‘Non-adoption, Abandonment, and Challenges to the Scale-Up, Spread, and Sustainability’ (NASSS) framework [13], qualitative methods will be used to assess challenges to the successful (or otherwise) implementation and sustainability of Hypertension-Plus. We will collect and analyse qualitative data via semi-structured interviews with implementation and clinical leads, and staff and patients associated with GP surgeries adopting the intervention, as well as anonymised OMRON customer support data logs.

### Data collection

#### Patient interviews

Semi-structured qualitative interviews will be held with approximately 20 patients as adopters of the intervention recruited via practice mail outs. The sample will include patients who were unwilling to adopt the intervention, patients who were willing but unable to maintain use, and patients who adopted the intervention and sustained their usage. Interviews will be used to understand patients’ experiences and views of the intervention. Interviews will be conducted by telephone or remote video and audio-recorded. Informed consent will be sought by the researcher before the start of all interviews.

### Healthcare professional interviews

Semi-structured qualitative interviews will be held with approximately 10–15 health care professionals (e.g., General Practitioners (GPs), nurses, pharmacists), representing all the study practices, as adopters involved in implementing the intervention in GP practices. Interviews will be conducted by telephone or remote video. Following informed consent, the researcher undertaking the interviews will invite health care professionals to reflect on their experiences of implementing the intervention, factors predicting or influencing intervention adoption, implementation and maintenance, and their thoughts on the impact of self-monitoring of BP on the target population.

### Implementer / clinical lead interviews

Semi-structured qualitative interviews will be held with approximately 15 implementation leads involved in rolling out Hypertension-Plus in two geographical areas and clinical leads from each of the participating GP surgeries. Leads will already have been identified at GP surgery / Primary Care Networks and via the National Association for Primary Care as part of the first phase roll out plan and will be invited by the study team. Interviews will be conducted by telephone or remote video. Following informed consent, the researcher undertaking the interviews will invite leaders to reflect on the wider context, their experiences of implementing the intervention at the organisational level (including their strategy and priorities for roll-out), any feedback from staff and their long-term view of sustainability.

### Omron customer support data logs

Records of customer support data in the form of anonymised support forms/email enquiries from Omron will be collected to gain insight into technological factors predicting or influencing intervention implementation and maintenance.

### Qualitative data analysis

Recordings, transcripts and customer support data will be uploaded to NVivo and analysed by members of the research team using the Framework Method [14]. The Framework Method has five stages: familiarisation; identifying a framework; indexing; charting; and mapping and interpretation. After listening to the recordings, reading transcripts and other written data and discussing impressions, thoughts and ideas in light of the research objectives, preliminary codes will be applied highlighting different aspects of the participants’ experiences, against illustrative extracts from the data. Framework categories will then be developed for the purpose of sifting and sorting the datasets informed by the seven domains in the NASSS framework to structure observations concerning factors predicting or influencing intervention adoption, implementation and maintenance, but also incorporating any additional issues pertinent to participants derived from the data. After piloting and refining the framework on a subset of data, the categories will be used to index each note and transcript in NVivo 12. The indexed data for each framework category will then be summarised and organised by the framework categories in chart form to facilitate within and between-case analyses to enable the mapping and interpretation of findings in light of the research question.

### Sponsor and permissions

The SHIP Study is sponsored by the University of Oxford, Clinical Trials and Research Governance, Joint Research Office, [name].

Ethics approval for the qualitative aspects for the qualitative aspects of the study was provided by Wales REC 4 (21/WA/0280). The quantitative cohort analyses were assessed by the sponsor as a service evaluation for which ethical permission was not required.

### Dissemination

Research outputs from this work will be published in peer-reviewed journals, presented at scientific conferences and via lay and social media (e.g., Twitter, blogs). ‘Patient friendly’ study summary documents and infographics will be made available to all participants at the end of the study via the study website and we will work with relevant patient groups (e.g. Blood Pressure UK) and health organisations (e.g. the primary care networks) to support dissemination to relevant groups and wider public.

## Discussion and conclusion

This mixed methods service evaluation aims to provide a greater understanding of the impact of initial implementation of the Hypertension-Plus digital intervention. It will allow comparison with the results from contemporary hypertension self-monitoring trials.

The results of this work will enhance understanding of self-monitoring of BP and enable better targeted and more effective implementation of SMBP. The qualitative process evaluation will give insight into the challenges to the successful (or otherwise) implementation and sustainability of the system.

**Fig. 1 Fig1:**
[figure not shown]
SHIP quantitative study procedures flow chart

## Data Availability

Quantitative data for this study are not available as access for the current analysis has been provided by agreements which preclude provision to third parties. Qualitative data are available from the authors upon reasonable request and with permission of the University of Oxford. Use of data will require approval by an independent review committee identified for this purpose and investigators requesting data will need to provide a written protocol including analysis plan and sign a data sharing/access agreement. Requests for Data Sharing should be directed to [contact].

## Abbreviations

BP: Blood pressure
CHD: Coronary heart disease
DBP: Diastolic BP
Efi: Electronic Frailty Index
EDA: Exploratory data analysis
GP: General Practitioner
HDL: High Density Lipoprotein
IMD: Index of Multiple Deprivation
NAPC: National Association for Primary Care
NHS: National Health Service
NICE: National Institute for Health and Care Excellence
NASSS: Non-adoption, abandonment, scale-up, spread, and sustainability
ORCHID: Oxford Royal College of General Practitioners Clinical Informatics Digital Hub
PCN: Primary care networks
QOF: Quality and Outcomes
REC: Research Ethics Committee
SQL: Structured query language
SD: Standard deviation
SNOMED CT: Systematised Nomenclature of Medicine clinical terms
SBP: Systolic BP
